## **Measures**

*Primary Outcome Measures:* The primary outcome measure will be 30-day point prevalence abstinence at 6 months post-intervention. This was also the primary outcome measure in our original trial and is a recommended outcome variable for tobacco cessation trials. Continued use of the same outcome variable allows us to merge the two datasets to allow an urban comparison group for the proposed trial.

*Content of baseline survey:* All items have been employed by us in previous studies, including our earlier RCT of mailed NRT in a largely urban sample. Participants will be asked: a) number of cigarettes smoked per day; b) level of nicotine dependence using the revised Fagerstrom test for nicotine dependence (Test-retest reliability = .78-.84); c) number and duration of past quit attempts; d) past use of NRT and other anti-smoking medications; e) use of stop smoking services; f) intent to quit smoking in the next 6 months and 30 days; g) quantity and frequency of alcohol consumption; h) illicit drug consumption (ever and past year); and i) a series of demographic characteristics. Items assessing the inclusion criterion of interest in receiving nicotine patches will be nested within items assessing use of stop smoking medications. In addition, as smoking impacts on health-related quality of life (HRQoL), the HRQoL will be additionally measured in all responders using the EUROHIS-QOL, an 8-item version of the World Health Organization HRQoL measure. Finally, questions about general health status will be asked which will include questions about health contraindications for NRT use.

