*Content of 6-month post-intervention follow-up survey:* Participants will be asked their current smoking status, including length of time without smoking in order to assess the primary outcome variable. Participants who have not quit will be asked how many cigarettes per day they currently smoke and their intentions to quit smoking; how soon after waking they smoke their first cigarette; and if, since their baseline interview, they have stopped smoking for even one day because they were trying to quit. Participants in the experimental group will be asked if they received free NRT and, if they did, to evaluate their experiences with NRT and to elaborate on their efforts to quit smoking. These questions will include items asking whether the participants used the NRT (none, some, all) and what they did with the NRT that they did not use themselves. These questions will be asked after the core smoking status outcome measures have been assessed. Participants in the control group will also be asked about their use of NRT but the questions will be framed to reflect purchase of NRT from sources other than this ongoing study.

Participants in both conditions will also be asked about their use of other smoking cessation aids and services, including electronic cigarettes, self-help/online methods, as well as participation and/or receipt of various forms of advice and counselling from family physicians, smoking cessation specialists, or other healthcare providers. As some individuals are known to initiate use of other tobacco products after stopping use of conventional cigarettes, such as cigars or non-combustible products such as smokeless tobacco or electronic cigarettes, participants who report smoking abstinence will be asked if they currently use other tobacco or nicotine containing products. This will allow us to examine whether people who quit cigarettes compensate with other forms of nicotine delivery.

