**Power calculations:** The power calculation was conducted to estimate the sample size needed to test the primary hypothesis that participants receiving the NRT package will display significantly greater quit rates (30 day abstinence) at 6-month follow-up as compared to those not offered the NRT package. Our secondary analysis of the rural participants in our earlier trial indicated a large effect (OR = 9.59; 8.9% 30-day abstinence rate at 6 months in those receiving NRT vs 1% in those not receiving the intervention). However, this estimate is not stable due to the small sample size (n = 200 in participants from rural regions; 95% CI 1.19 to 77.16). As such, we have reduced the anticipated size of the impact of the intervention to 75% to generate the sample size estimate for the current proposal (i.e., OR = 7.1; 6.7% 30-day abstinence rate at 6 months in those receiving NRT vs 1% in those not receiving the intervention). This will allow for the likely possibility that, while the impact of the NRT intervention is large in rural regions, it may not be as large as was observed in the secondary analyses. The power analysis was based on Monte Carlo simulations. Randomly distributed dropouts were also included in the simulations, at a rate of 20%; thus accounting for the 20% attrition expected between baseline and 6-month post-intervention follow-up based on earlier trial findings. Quitting smoking was the binary outcome, measured as 30-days abstinence. A sample of 290 participants per group (intervention versus control) is needed in order to obtain 80% power with 95% confidence interval. Further, analyses from our earlier trial established that 50.1% of participants from rural regions would be interested in receiving nicotine patches (and would use it within a week to quit), leading to a baseline survey needed of 1,138 participants. Finally, results from our earlier trial found that 10% of those recruited at baseline were not eligible because of reporting a health condition

contraindicating NRT use without the supervision of a doctor. Thus, in order to conduct this trial, we would need to recruit 1,252 participants for the baseline survey in order to have sufficient participants for the trial (1,138 X 110%).

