**Step 2:** Tests to identify factors that systematically vary between individuals, and between municipalities, that explain the size of the impact of the NRT intervention on self-reported 30-day abstinence at 6-month follow-up. For these analyses, the data from urban comparison sample will be combined with the data collected in the current project of rural participants in order to allow for stronger tests. We have *pre-specified two hypothesized municipal factors* and predict that prevalence of smoking at the municipal level, and availability of health services in the municipality, will be related to the size of the impact of the NRT intervention. The multi-level logistic regression models constructed will include municipal-level sampling frame data (province or territory region of Canada), and municipal level smoking prevalence and health services availability data to determine the size of the impact of the intervention with the individual-level outcome data. Individual demographic (including participant gender) and severity of smoking characteristics will be included in order to identify individual-level factors relevant to the impact of the intervention.

*Secondary analyses* will add other characteristics of the municipality [average SES, population density, tobacco retailer density, NRT distributor (e.g., pharmacy, grocery store) density] to identify other contextual factors that may be important in determining the size of the impact of the NRT intervention. Additional secondary analyses will assess the effects of NRT and other predictors on relevant dependent measures pertaining to those who have not quit. These analyses will include multilevel models predicting the number of cigarettes smoked, intentions to quit, and whether participants have quit temporarily during a given time-period.

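### The additional secondary models estimate effects of NRT only among participants who have not quit, which conditions on the primary outcome

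*Protocol*

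**What the plan says.** The Protocol's Analysis Plan, under Secondary analyses, ends with: "Additional secondary analyses will assess the effects of NRT and other predictors on relevant dependent measures pertaining to those who have not quit". The closing words, "relevant dependent measures pertaining to those who have not quit", set the subset. It lists the models as "multilevel models predicting the number of cigarettes smoked, intentions to quit, and whether participants have quit temporarily during a given time-period".

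The description of the 6-month follow-up survey applies the same restriction when the data are collected: "Participants who have not quit will be asked how many cigarettes per day they currently smoke and their intentions to quit smoking". The item on whether, since baseline, "they have stopped smoking for even one day because they were trying to quit" stands in the same list.

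The variable that defines this subset is the trial's main endpoint: "The primary outcome measure will be 30-day point prevalence abstinence at 6 months post-intervention". The Power calculations expect it to differ strongly by arm: "OR = 7.1; 6.7% 30-day abstinence rate at 6 months in those receiving NRT vs 1% in those not receiving the intervention".

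The Analysis Plan gives no version of these models in all participants, no adjustment for selection and no caution about reading the arm contrast causally.

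**The concern.** Randomization makes the two arms comparable at baseline. It does not make the continuing smokers of one arm comparable with those of the other, because the intervention is expected to change who is still smoking at six months. If the patches work as planned, more of the successful participants leave the intervention arm's subset than leave the control arm's. A difference between the remaining smokers then mixes any effect of the patches with this unequal removal.

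The protocol calls the result an effect of NRT. At stake is whether a reader is told that the patches did little, or did harm, for quit attempts or consumption when the figure partly reflects who was left in the comparison. This would happen even with complete follow-up, and a larger sample would not remove it.

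**Working it through.** **Inputs from the Protocol.** Quit rates 6.7% vs 1%, 290 per group, 20% dropout (Power calculations); 1:1 allocation (Randomization).

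**Assumptions, not in the Protocol.**
- Not having quit means not meeting the 30-day abstinence outcome.
- Every 30-day abstainer counts as having stopped for at least one day.
- The planned quit rates and the 20% loss apply equally among those followed in each arm.
- Between 30% and 50% of all followed participants stopped for at least one day.
- Cigarettes per day at baseline have mean 19 and SD about 7.3.

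**The plan's own figure.** "A sample of 290 participants per group (intervention versus control) is needed in order to obtain 80% power with 95% confidence interval". After 20% loss, 290 × 0.8 = 232 per arm. A simulation of 20,000 trials at 6.7% vs 1%, with a two-sided 5% Wald test of the log odds ratio, gives 80.9% power. The planned size is reproduced, so 232 followed per arm is used below.

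**Size of the subset.** Intervention: 232 × 0.933 ≈ 216. Control: 232 × 0.99 ≈ 230.

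**Temporary quitting.** If a proportion *a* of an arm stopped for at least one day and a proportion *q* of that arm quit, the proportion seen among non-quitters is (*a* − *q*)/(1 − *q*). With no true difference between arms:

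| True rate, both arms | Intervention non-quitters | Control non-quitters | Difference | SE | Difference/SE |
|---|---|---|---|---|---|
| 30% | (0.30 − 0.067)/0.933 = 25.0% | (0.30 − 0.01)/0.99 = 29.3% | −4.3 points | 4.2 | 1.0 |
| 40% | (0.40 − 0.067)/0.933 = 35.7% | (0.40 − 0.01)/0.99 = 39.4% | −3.7 points | 4.6 | 0.8 |
| 50% | (0.50 − 0.067)/0.933 = 46.4% | (0.50 − 0.01)/0.99 = 49.5% | −3.1 points | 4.7 | 0.7 |

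The SE is √[*p*₁(1 − *p*₁)/216 + *p*₀(1 − *p*₀)/230]. At 40% the apparent odds ratio is (0.357/0.643)/(0.394/0.606) ≈ 0.85, where the true value is 1.

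**Where the sign changes.** The apparent difference is zero when the intervention rate equals 0.067 + 0.933 × (*a* − 0.01)/0.99. For control rates of 30%, 40% and 50% this is 34.0%, 43.5% and 52.9%. True benefits below about 4.0, 3.5 and 2.9 points would therefore appear as harm.

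**When there is a real benefit, from a 40% control rate.**
- True 45.7% (+5.7 points, OR 1.26): non-quitters show (0.457 − 0.067)/0.933 = 41.8% vs 39.4%, or +2.4 points, OR 1.105.
- True 50% (+10 points, OR 1.50): non-quitters show 46.4% vs 39.4%, or +7.0 points, OR 1.33.

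**Cigarettes per day, with no effect of the patches except through quitting.**
- All followed participants, quitters counted as 0: if quitting is unrelated to heaviness, the difference is about −19 × (0.067 − 0.01) ≈ −1.1 per day. If lighter smokers quit more readily, simulation gives down to about −0.8.
- Non-quitters only: about 0 if quitting is unrelated to heaviness, +0.15 to +0.33 if lighter smokers quit more, and about +0.5 in the extreme case where the lightest quit first. The SE is about 0.7. If heavier smokers quit more, the sign would be the other way.

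**The case against.** **These are minor analyses.** They carry no hypothesis and no power. The primary analysis counts everyone randomized, with those lost taken as smokers; the moderator models use abstinence; and the other secondary analyses, which add municipal characteristics, are not restricted to non-quitters. All of this stands. A reader might infer that the trial's secondary comparisons in general are compromised, and the document does not support that.

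**The question may be descriptive.** Whether continuing smokers cut down or intend to quit is a fair question, the population is openly named, and intention to quit has no natural value in a quitter. This supports keeping the non-quitter results. It does not support calling their arm contrast an effect of NRT.

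**A 30-day abstainer has not quit temporarily.** If the outcome means stopping and then relapsing, the shifts computed above compare two different outcomes. The survey item, however, asks about any stop of at least one day, and every 30-day abstainer has gone at least that long without smoking. Under the narrower meaning the outcome can occur only in those who did not stay quit, so the contrast among non-quitters is still not a randomized one.

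**The size rests on an assumed rate and lies within noise.** Correct: the Protocol gives no rate of stopping, and the shift is about one standard error or less. It is also tempting to say that the restriction hides over half of a real benefit. That holds for the 45.7% example, but at a true 50% vs 40% about 70% of the log odds ratio is kept.

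**An unseen SAP may settle this.** A companion analysis could be specified there, and its absence is not the criticism. The Protocol itself states both the subset and the aim of estimating an effect.

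**Conclusion.** The concern holds for the additional secondary models of cigarettes smoked, intentions to quit and temporary quitting, and for nothing else in the Analysis Plan. Those models condition a treatment contrast on the primary outcome.

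For temporary quitting the direction is clear under the stated assumptions: a shift of about 3 to 4 points against the patches at 6.7% vs 1%, enough to change the sign of a true benefit smaller than that, but only about 0.7 to 1.0 standard errors. It would be larger if the quit rates differed more by arm.

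For cigarettes per day the main loss is that the reduction achieved through quitting (about 0.8 to 1.1 per day under the assumed distribution) drops out. A reader might infer that the remaining contrast must also be biased against the patches. The documents do not support that, because its direction depends on who quits, and in the cases examined it stays below one standard error. No size can be given for intention to quit.

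**What to change.** Reword the last part of Secondary analyses along these lines:

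- For cigarettes per day and for any stop of at least one day since baseline, estimate the arm effect in all participants followed up at six months. Code quitters as 0 cigarettes per day and as having stopped.
- State a missing-data approach for those lost. A reader might ask for all randomized participants, but the expected 20% who are lost give no answers to these items, and counting them as smokers supplies neither a number of cigarettes nor a record of a stop.
- Report results among non-quitters, including intention to quit, by arm as description, without a treatment-effect claim. Ranking quitters above every level of intention on one scale is possible, but it is a debatable composite and is not needed.

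The cost is a little more analysis and a missing-data statement. No new data are needed, because the follow-up survey already records smoking status and time since last smoking. The drawback is that the cigarettes-per-day result will partly restate the primary outcome, and the report should say so.

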**Discussion**

Preventing cancer through reducing smoking rates is a cornerstone of improving the health of Canadians. Mass distributions of nicotine patches have become a major prevention initiative in Canada. The proposed trial will combine an RCT with a municipal linking strategy in order to systematically study how social and environmental factors that vary at the municipal-level will impact on the efficacy of this health intervention. What if the significant resources devoted to nicotine patch distribution were better targeted to regions where they could have the greatest impact and further, help address the health disparities associated with rural regions of Canada? This trial will allow us to answer this question, promising greater success in preventing cancer through promoting tobacco cessation.

